#### Qualitative study

Few studies have used qualitative methods to explore patients’ experiences of esophageal cancer [7]. Only one recent qualitative paper is available that focuses on dysphagia in patients with esophageal cancer [26] and no qualitative papers on stent placements in esophageal cancer patients could be traced. Analysis of available literature demonstrates patients shared concerns around issues of coping. How these were constructed and relayed differed by narrative, but the thematic finding demonstrates the value of researching patients’ experiences as an outcome in itself. Drawing on the experiences of patients, the ROCS qualitative study will focus on the following objectives: exploring patients’ motivation for participating in the trial, exploring reasons for refusing the trial, assessing patient experience and perceptions of each arm of the trial, providing patient outcome data in order to assess the feasibility of the trial design, and identifying potential improvements to the recruitment process. It is essential that the qualitative study takes place in the pilot phase of the trial in order to address challenges to recruitment prior to the continuation of the main trial.

Subsequent to the consent process the interviews will be conducted at either the participant’s home or an alternative quiet location. If a face to face interview is not possible, telephone or video-linked interviews are allowed where appropriate. It is anticipated that the interview will take between 30 minutes and one hour, however it may be stopped earlier if a patient appears fatigued or becomes unwell.

The qualitative component of ROCS aims to recruit a sample size of 12 to 20 patients for the experimental arm of the trial, and 6 to 10 patients for the control arm, with 6 to 10 non-consenting patients expected to consent to interview on reasons for not participating in the main trial. Non-consenters to the clinical trial will be interviewed on one occasion whereas those participating in the clinical trial will be interviewed three times; in weeks one and four to capture initial decision-making thoughts, and again at week eight to explore experiences of the intervention process and perceptions of any benefits or negatives experienced thus far.

Analysis of the qualitative interviews will be undertaken using an Interpretative Phenomenological Analysis (IPA) framework [27, 28]. IPA seeks to explain the meaning that events have for participants based on their own, everyday social reality. Each interview will initially be analyzed in isolation and focus on exploring how participants have interpreted their experiences. The analysis will be undertaken using a coding framework that will be developed alongside the search for emerging themes that are common across the transcripts.

The results of the analysis will be discussed and presented with the use of narrative extracts to support and illustrate claims and findings of the analysis. It is intended that the TMG will analyze the results to assess any recruitment challenges that may have been identified, and respond with potential alterations to the trial design. The findings of the qualitative study will also, where appropriate, be used to complement the full trial report.

### Sample size considerations

In a population with a median survival of approximately four months, an increase in median time to deterioration in self-reported dysphagia of four weeks is considered clinically meaningful. This is based on previous results in Homs *et al*. [9] and expert multidisciplinary and service user opinion. A survey of participating centers demonstrated clinician accord with this. Time to event will be calculated from the time of stent insertion to the time of deterioration (of 11 points or more) or death. Sample size is therefore based on a time to event analysis, to detect an increase in median time to deterioration in self-reported dysphagia of four weeks: from 12 to 16 weeks (equivalent to a hazard ratio (HR) of 0.75 and a difference in 12-week event rate of 50 versus 60%). Recruitment time will be 4.25 years with a six-month follow-up after the final patient is recruited. For 80% power with an alpha of 0.05 based on a two-sided log rank test, 198 patients per arm will be required, with 396 in total, which is a total of 384 events. Assuming 20% attrition, a total of 496 patients will be required. The degree of attrition is set at this higher level because of the vulnerability of the patient population.

### Statistical analysis

All analyses will be performed on a full intention-to-treat basis, that is, all patients randomized will be included, and all patients will be analyzed according to their allocated group whatever treatment they receive. Descriptive statistics of the patient characteristics within each treatment group will be presented (including a summary of the type of the treatment each patient actual received).

The main analysis will compare the time until self-reported dysphagia progression between the two groups using Kaplan-Meier curves and the log-rank test. The final analysis will take place when 384 events (deterioration or deaths) have been reported, which is expected to be approximately six months after accrual closes. Kaplan-Meier curves and log-rank tests will also be used to compare the two groups on the secondary outcomes of overall survival. It is possible the data for the secondary endpoints (such as toxicity) may be mature enough for analysis and presentation before the main overall survival primary endpoint. The secondary outcomes of proportions of morbidities and re-intervention rates will be compared using a chi-square test. The area under the curve of HRQoL scores will be compared using t-tests adjusted for follow-up interval and survival. The main analysis will be carried out when the required number of events has been reached (see proposed sample size above).

No formal subgroup analyses are planned to look at differences in primary and secondary endpoints between treatment groups within specific groupings based on patient characteristics. However exploratory analysis will be conducted to explore whether there is any consistent benefit from using radiotherapy after a stent in different subgroups by creating HR plots and carrying out tests for interaction or trend based on chi-square analysis. The statistical package STATA (StataCorp LP, Texas, USA) will be used for all analysis and a statistical analysis plan will be written before the data is analyzed.

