### Study interventions

The SEMS procedure for both arms will be as follows: a stent will be inserted, following the decision by the MDT to proceed with stenting as the primary treatment for the dysphagia. Insertion will be in accordance with the standard procedures of the treating centre. The length and type will be determined by the responsible clinician. The following will be recorded: whether the stent is inserted under sedation or general anaesthetic, whether dilatation is required before or after stent insertion, and whether radiological imaging is used. Where possible the length of stent will be chosen to ensure that at least 2 cm of normal esophagus is covered by the stent above and below the tumor stricture. Where necessary, more than one stent may be deployed. A post-insertion esophagogram may be used to confirm stent position and exclude perforation.

Esophageal dilatation that is used as part of the center’s normal procedure for stent insertion is permitted. The trial should not be offered to patients who are deemed to need or are offered routine endoscopic treatment of the tumor (such as endoscopic laser therapy) in the immediate peri-stenting period, unless an emergency situation arises that requires such a procedure. Brachytherapy or external beam radiotherapy should not be planned to be given routinely after stent insertion for those patients in the control arm. Patients will be stratified according to the prior use of systemic chemotherapy.

External beam radiotherapy treatment for the intervention arm will begin within four weeks after stent insertion. Radiotherapy will be delivered using a simple technique (usually a parallel opposed pair of beams) with either a dose of 20 Gy in five fractions over one week, or 30 Gy in 10 fractions over two weeks, prescribed to the mid-point of the irradiated volume, using daily fractionation and the center’s normal radiotherapy treatment procedures. The dose and fractionation schedule chosen will be at the discretion of the treating clinical oncologist. Treatment will normally be received as an outpatient.

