#### Morbidity

Overall length of hospital stay, complication rates, number of blood transfusions, and re-intervention rates will be gathered from case notes and captured in the case report forms. Early complications will be defined as those occurring within seven days of the intervention, and late complications will be defined as those occurring more than seven days after the intervention. Standard definitions of stent complications will be clearly described in the protocol.

Toxicity data will be scored using the National Cancer Institute CTCAE v4.03 and the Radiation Therapy Oncology Group acute/late questionnaire at baseline, during treatment, and at the pre-specified time points on follow-up. SAEs will be monitored in real-time by the chief investigator and trial management group (TMG.) Data will also be collected on symptom burden including pain, eating restrictions, and physical functioning via the EORTC QLQ-C30 and QLQ-OG25 scales.

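### The rule that every analysis is by intention to treat also covers toxicity, so patients allocated radiotherapy who never start it dilute the reported radiotherapy toxicity

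*Protocol article*

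**What the plan says.** The Statistical analysis section of the protocol article opens with a rule for every outcome: "All analyses will be performed on a full intention-to-treat basis, that is, all patients randomized will be included". It adds that "all patients will be analyzed according to their allocated group whatever treatment they receive". No outcome is exempted.

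Toxicity falls under this rule. The same section says of it: "It is possible the data for the secondary endpoints (such as toxicity) may be mature enough for analysis and presentation". The Morbidity section, under secondary outcomes, has toxicity scored by CTCAE and the RTOG questionnaire "at baseline, during treatment, and at the pre-specified time points on follow-up". The planned test is given as: "The secondary outcomes of proportions of morbidities and re-intervention rates will be compared using a chi-square test". The article does not name a separate test for toxicity. Its place under Morbidity suggests that the chi-square test is meant to cover it.

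Treatment received appears once, in the descriptive tables: "including a summary of the type of the treatment each patient actual received". No toxicity analysis uses it.

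Three features of the design make non-start possible. Recruitment and randomization places allocation before stent insertion. Study interventions says: "External beam radiotherapy treatment for the intervention arm will begin within four weeks after stent insertion". Sample size considerations describes the setting: "In a population with a median survival of approximately four months".

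**The concern.** Non-receipt of the allocated treatment shrinks the difference between arms. For a superiority claim on efficacy that is conservative. For a harm caused by the added treatment it works the other way: the excess looks smaller than it is among those treated, and a test is more likely to miss it.

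A patient allocated radiotherapy who never has a fraction cannot have radiation toxicity, yet counts in that arm's denominator. The summary of treatment received will show how many such patients there are, but it leaves the toxicity rate unchanged.

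The protocol itself expects a radiation effect: under Primary outcome measure it anticipates temporary esophagitis after radiotherapy and wants it recorded. A patient weighing palliative radiotherapy needs the risk among people who receive it, and the stated rule does not produce that figure.

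**Working it through.** **The plan's own figures.** The article gives no figure for toxicity, so only the arm size can be checked. For HR 0.75, two-sided 5% and 80% power, Schoenfeld's formula gives 380 events and Freedman's 385, against the stated 384. Inflating 198 per arm for 20% attrition gives 198 / 0.8 = 247.5, rounded up to 248 per arm and 496 in total, as stated. This point leaves the primary sample size untouched.

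**Step 1: can non-start happen by death alone?** Assume exponential survival with a median of four months (17.4 weeks). The share dead by week w is 1 − 2^(−w/17.4).
- Week 2: 7.7%
- Week 4: 14.7%
- Week 4 with medians of 13 to 21.7 weeks: 19% to 12%

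These are rough markers and do not estimate the non-start share. Two eligibility criteria lower them: expected survival of at least 12 weeks, and ability to attend for radiotherapy. Starting before week 4 lowers them too. Refusal and decline without death raise the share. The working range of 10% to 30% is an assumption.

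**Step 2: the dilution.** Let f be the share of the radiotherapy arm that never starts, p1 the toxicity rate if irradiated and p0 the rate if not. Assume that non-starters have the background rate p0 and that no control is irradiated. Then:

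arm rate = (1 − f)·p1 + f·p0

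reported excess = (1 − f)·(p1 − p0)

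**Step 3: illustration.** Take p1 = 20% and p0 = 10% (assumed), with n = 248 per arm. Power is for a two-sided 5% test of two proportions, Φ[(Δ − 1.96·SE0)/SE1]. SE0 uses the pooled rate and SE1 the separate rates.

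| f | Radiotherapy-arm rate | Reported excess | Power |
|---|---|---|---|
| 0 | 20% | 10 points | 88% |
| 10% | 19% | 9 points | 81% |
| 20% | 18% | 8 points | 73% |
| 30% | 17% | 7 points | 63% |

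Check of the 10% row:
- SE0 = √(2 × 0.145 × 0.855 / 248) = 0.0316
- SE1 = √((0.19 × 0.81 + 0.10 × 0.90) / 248) = 0.0314
- (0.09 − 1.96 × 0.0316) / 0.0314 = 0.89, and Φ(0.89) = 0.81

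**Step 4: control radiotherapy.** The article says only that it should not be planned as routine. If a share g of controls received it, the reported excess would become (1 − f − g)·(p1 − p0). The direction is the same; g is not given.

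**The case against.** **Left to the analysis plan.** This is a condensed article that promises a statistical analysis plan, and safety sets are usually defined there. That would settle the matter if the article were silent. It is not silent: it states a rule for all analyses, and that rule reaches toxicity. A reader might go further and infer that the text forbids any table by treatment received. It does not say so, and a supplementary table could sit beside the intention-to-treat one. The defect is that the only stated rule gives the diluted figure.

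**Intention to treat is a valid choice.** The trial is pragmatic, and toxicity by allocation gives the harm of a policy of adding radiotherapy, on the same footing as its benefit. This stands, and it is why that table should stay. It also stands for complications and re-interventions. The Background hopes radiotherapy will ameliorate late problems such as hemorrhage and overgrowth, so for those outcomes dilution can be conservative.

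**Non-starters counted as irradiated and free of toxicity.** A reader might infer this, but the text does not support it. Patients are grouped by allocation, and the treatment they received is summarised. CTCAE is scored in everyone at baseline, week 1, week 4 and four-weekly, so non-starters keep their stent and disease toxicity. Giving them zero toxicity would cut the excess to 8, 6 or 4 points at 10%, 20% or 30% not starting; nothing in the article justifies that.

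**The size is assumed.** This stands. At 10% not starting, the loss is one point and power is still 81%. The article claims no power for toxicity. Real-time monitoring of serious adverse events is also planned, so safety oversight does not depend on this comparison.

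**Conclusion.** The point holds as a matter of direction. The stated rule covers toxicity and the design makes some non-start likely, so the radiotherapy arm's radiation toxicity rate, and its excess over control, are diluted towards no harm. The treatment-received summary does not correct this.

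The size cannot be derived from the article. The fall from 10 points to between 9 and 7, and in power from 88% to between 81% and 63%, rests on four assumptions: 10% to 30% not starting, toxicity of 20% against 10%, background toxicity in non-starters, and no irradiated controls. A reader might infer that the non-start group is large, or that the intention-to-treat toxicity comparison is invalid. The article supports neither: it gives no non-start share, and the allocated comparison properly answers the policy question. Efficacy, survival and the primary sample size are unaffected. The change is worth making because it is cheap and uses data already planned.

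**What to change.** In Statistical analysis, limit the intention-to-treat-only rule to efficacy, survival, quality of life, re-interventions and complications. For toxicity, keep the intention-to-treat table and add:

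*Toxicity will also be reported among patients who received at least one fraction of radiotherapy, with the number allocated but not started, beside stent-only patients who received no radiotherapy, as a supportive non-randomized comparison.*

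Do not require only the controls to be alive at week 4. Radiotherapy may start earlier than that, so such a rule would remove early deaths from the controls but keep them among the irradiated. Any alignment of the start of follow-up must apply alike to both groups and must not discard acute toxicity before week 4.

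The cost is one extra set of tables from data already planned, with no change to treatment or sample size. The downside is selection: patients who start radiotherapy are those fit enough to do so, and the comparison does not adjust for this. It therefore supplements the intention-to-treat table and does not replace it.

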### Recruitment and randomization

Eligible participants will be identified and approached in secondary care including cancer centers and district general hospitals. The patient’s consent to participate in the trial will be obtained prior to any trial-related procedures, which includes the insertion of a stent, and after a full explanation of the treatment options has been given. Consent will be taken by an appropriately trained research nurse or delegate. Patients who consent to randomization will also be asked to consent to NHS Information Centre flagging so that the date and cause of death can be collected without longer term follow-up. This will be optional and additional to the standard informed consent.

Patients who decline to participate in the main study, as well as participants who enter the main study, will be asked whether they consent to the storage of their contact details so that a qualitative researcher may contact them to invite them to participate in a qualitative interview about the reasons behind their decision not to participate in the main trial, or of their experiences of the interventions, as appropriate. Patients who agree to the storage of their contact details will be asked to sign the appropriate section of the main consent form. At this time, they will also be given a separate qualitative interview patient information sheet and consent form to take home and read. The qualitative researcher will collect consent for conducting the interview immediately prior to commencement of the interview, using the qualitative interview consent form.

Patients will be randomized centrally by the Wales Cancer Trials Unit prior to stent insertion using the method of minimization, which includes a random element. Patients will be stratified for a number of clinically important factors. The randomization allocation ratio for control to intervention arms will be 1:1 and the embedded qualitative component of the study will also explore patients’ perceptions and experiences of the randomization process.

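### The primary and overall survival log-rank tests take no account of the minimization factors; the stated 80% power is sound, but the test is conservative and forgoes power if those factors are prognostic

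*Protocol article*

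**What the plan says.** Under Recruitment and randomization, the protocol article allocates patients centrally "using the method of minimization, which includes a random element", and adds: "Patients will be stratified for a number of clinically important factors". The number of factors and their names are not given there. One is named under Study interventions: "Patients will be stratified according to the prior use of systemic chemotherapy". Allocation is 1:1.

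Under Statistical analysis, the main analysis will "compare the time until self-reported dysphagia progression between the two groups using Kaplan-Meier curves and the log-rank test". Overall survival is compared in the same way. No stratification or covariate adjustment is mentioned for either. The same paragraph does state adjustment for the quality-of-life area-under-the-curve comparison (for follow-up interval and survival).

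Under Sample size considerations, the design uses the same test: "For 80% power with an alpha of 0.05 based on a two-sided log rank test, 198 patients per arm will be required". The effect is a rise in median time to deterioration "from 12 to 16 weeks (equivalent to a hazard ratio (HR) of 0.75"), and the size is "with 396 in total, which is a total of 384 events", raised to 496 for 20% attrition.

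**The concern.** Minimization forces the arms to be alike on the chosen factors. If those factors also affect time to deterioration or death, the difference between arms varies less from trial to trial than it would under simple randomization. A plain log-rank test does not use this. Its variance is computed as if the factors were free to differ between arms, so it is too large, and the test rejects less often than its nominal level. A test that accounts for the factors restores the level and gains power from the same patients.

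Recruitment is planned over 4.25 years in a frail population with a 20% attrition allowance, so power that costs no patients is worth having. A second stake is discipline. If adjustment is not settled in advance, the adjusted and unadjusted results could differ at the 5% boundary with no agreed rule on which one counts.

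**Working it through.** **1. Reproduce the stated design as a plain log-rank test.** Inputs from Sample size considerations: HR 0.75, two-sided alpha 0.05, 80% power, accrual 4.25 years, follow-up 6 months, 20% attrition. (1.960 + 0.842)² = 7.849.

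- Schoenfeld: 4 × 7.849 / (ln 0.75)² = 31.396 / 0.08276 ≈ 379.4, so 380 events.
- Freedman: 7.849 × (1.75 / 0.25)² = 7.849 × 49 ≈ 384.6, so 385 events. Stated: 384.
- Power at 384 events: Schoenfeld Φ(√384 × 0.2877 / 2 − 1.960) = Φ(0.859) = 80.5%; Freedman Φ(√384 × 0.25 / 1.75 − 1.960) = Φ(0.839) = 79.9%.
- Patients: with exponential times, λ = ln 2 / median, accrual length R and minimum follow-up F, P(event) = 1 − e^(−λF)(1 − e^(−λR)) / (λR). This gives 0.983 (median 12 weeks) and 0.966 (16 weeks), mean 0.975. Freedman's 385 events then need about 395 patients. Stated: 396.
- Attrition: 396 / 0.8 = 495. Stated: 496.

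The stated figures hold.

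**2. Simulate plain against stratified log-rank.** 396 patients, arms balanced within strata, exponential times within strata, 50/50 binary factors, accrual and follow-up as stated. The factor strengths are assumptions. There were 4,000 to 5,000 simulated trials per scenario (Monte Carlo error about 0.6 points for power and 0.3 for type I error). A range shows two runs of one scenario.

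| Assumed factors | Plain, type I error | Power if within-stratum HR is 0.75: plain / stratified | Power if arm-level HR is 0.75: plain / stratified |
|---|---|---|---|
| None prognostic, 4 strata | 5.5% | 80–81% / 79–80% | same case |
| One, HR 1.5 | 4.6% | 78% / 80% | 80% / 83% |
| One, HR 2 | 4.1% | 73–74% / 79–80% | 80% / 86% |
| Two, HR 1.5 each | 4.3% | 75% / 79% | 80% / 84% |
| Two, HR 2 each | 3.5% | 65–67% / 78–79% | 79% / 89% |

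The power forgone is about 2, 6, 4 and 12 to 13 points on the within-stratum reading, and about 3, 6, 4 and 10 points on the arm-level reading. The stratified test's type I error was 4.8 to 5.2% in the four prognostic scenarios. The 4.6% for one factor of HR 1.5 is within simulation error of 5%; the 3.5% for two factors of HR 2 is clearly not.

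**3. Which HR is 0.75?** The two readings differ because the HR is not collapsible. A within-stratum HR of 0.75 corresponds to arm-level HRs of 0.756, 0.767, 0.763 and 0.780 in the four prognostic scenarios. The medians do not settle the matter. With exponential times in each stratum, multiplying every hazard by 0.75 stretches all times by 1 / 0.75 = 4/3, so an arm median of 12 weeks becomes 16 while the arm-level HR is slightly above 0.75. The protocol's event calculation, however, takes the HR as holding between arms, and its figures agree on that reading.

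**4. Too many strata.** With non-prognostic factors, full cross-classification into 40 strata (396 / 40 ≈ 10 patients each) lowers power to about 70%, and 80 strata (about 5 each) to about 65%, against about 80% for the plain test. These stratum counts are assumptions.

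The simulation covers the primary endpoint and a stratified log-rank test. The Cox model and overall survival were not simulated; the same argument applies to them in kind.

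**The case against.** The strongest reply is that this is a condensed article which announces a statistical analysis plan, and that adjusting for minimization factors is a detail such a plan may supply. The article does not call the test unstratified, and it calls the factors clinically important, not prognostic. All of that is true, and the analysis plan may well deal with it. But the article does more than stay silent. It names the primary test, sizes the trial on that test, and mentions adjustment elsewhere in the same paragraph, so the plain reading is the natural one.

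A second reply is that sizing and analysis use the same test, so nothing promised is lost. This stands. A reader might infer that the trial is underpowered, or that minimization bought power which the analysis throws away. The documents do not support that: plain power below 80% arises only if 0.75 is the within-stratum HR and the factors are prognostic, and the protocol states neither.

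Nor should a reader infer that the unadjusted HR is biased. It lies nearer 1 than the within-stratum HR because it is a different estimand. Finally, extending the point to every secondary outcome goes beyond what was computed, and the quality-of-life comparison already carries some adjustment.

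It is also true that stratifying on every factor could do harm. That bears on the choice of remedy, not on the point itself.

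**Conclusion.** The point holds as a modest one about efficiency and type I error calibration; it is not a sample-size error. For one or two balanced binary factors of HR 1.5 to 2, the plain log-rank test runs at about 3.5 to 4.6% instead of 5% and forgoes about 2 to 13 points of power. If the factors are not prognostic, using a few of them costs about one point or less. The error is in the conservative direction, so a positive result from the plain test would not be undermined.

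The size rests on assumed prognostic strengths, 50/50 factors and exact balance within strata. Minimization with a random element only approximates that balance. The true size cannot be derived from the protocol.

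**What to change.** State in the analysis plan, before any data are analyzed:

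- The primary analysis is a Cox model with treatment arm and the minimization factors, listed by name, as covariates. The treatment effect is tested at the two-sided 5% level and reported as an adjusted HR with 95% CI.
- Alternatively, use a log-rank test stratified on only a few pre-named factors. Do not cross-classify all of them, particularly if center is among them (the article does not say).
- Overall survival is analyzed in the same way.
- Kaplan-Meier curves stay as the display, and the plain log-rank test becomes a sensitivity analysis.
- The adjusted HR is labelled as conditional on the factors, so that it is not compared directly with an unadjusted HR.

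The cost is wording only. The factors are known for every patient at randomization, and neither the 384 events nor the 496 patients need to change.
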